### Randomization and blinding

In the study, stratified randomization will be adopted. Prior to randomization, all qualified participants will be classified according to uterine size by ultrasonic measurement (class A = uterine size smaller than 10 cm of the maximum diameter, class B = uterine size between 10 and 15 cm of the maximum diameter, and class C = uterine size larger than 15 cm of the maximum diameter), since uterine size is the primary determinant of the operation time for hysterectomy.

The research assistant will acquire a randomized timetable generated by a computer. Trial participants and research assessors will be blinded to the information of group allocation, as ensured by sequentially numbered, opaque and sealed envelopes. The research assistant will be excluded from the results evaluation and data collection. Patients will be blinded to distribution and intervention information. In case of serious adverse events, the outcome evaluator will inform the surgeon to evaluate whether it is related to the intervention and carry out further treatment without unblinding the patient.

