**Methods:**

Patients who undergo total hysterectomy will be enrolled in this RCT. Stratified randomization will be performed according to uterine size (< 10 cm, 10–15cm, ≥ 15 cm). The participants will be divided into the chopstick technique group or cross technique group to undergo laparoendoscopic single-site total hysterectomy (LESS-TH), and then the perioperative and postoperative data, including the total operation time and other times, transfer rates, estimated blood loss, surgeon fatigue, intraoperative and postoperative complications (within 8 weeks after surgery), health-related quality of life (EQ-5D) scores, postoperative hospital stay, and hospitalization expenses, will be evaluated. The primary outcome is the operating time for total hysterectomy under LESS, and the other outcomes are secondary outcomes.

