### Measurement and data collection

#### Outcome measures

The following baseline characteristics of patients will be documented: age, BMI, volume of the uterus, concomitant medications, EQ-5D scores, and anesthesiology scores (ASA).

B. The specific process for follow-up (Table 1):

During the screening period (before surgery), surgical indication, inclusion and exclusion indicators, gynecological check results will be investigated.

The collection of data on the day of surgery will include the successful removal of the uterus by the technique as randomized; conversion to laparoscopy or laparotomy; the total operation time (classified as the single-port establishment time, pelvic-abdominal adhesion release time, total hysterectomy time, specimen removal time, and stump suture time); estimated blood loss; intraoperative complications (including blood transfusion, vascular repair, bowel surgery, bladder surgery, ureter operation); and surgeon fatigue.

On the day of discharge, data on hospitalization expenses and the postoperative hospital stay will be collected by the research assessor.

During the 8 weeks after the intervention, postoperative complications (such as a second operation, infection, urogenital tract injury, intra-abdominal hemorrhage, incision hematoma, incision infection) will be recorded and rated by the Clavien–Dindo classification method. Health-related quality of life (EQ-5D) will be assessed again at 8 weeks (Table 2).

**Table 2 Tab2:** Patient’s characteristics and data collection

Timepoint	Study period							
	Enrollment	Allocation	Post-allocation					Close-out
		0	Pre-operation	Operation	Post-operation	Discharge	After 8 weeks	

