### Statistical analysis

The research assistants will send nonblinded data to a statistician for analysis, who will remain blinded to the other investigators until all data analysis is complete. The data will be analyzed with SPSS version 25.0 software. Continuous variables that are normally distributed will be analyzed according to the means and SDs, and discrete variables that are nonnormally distributed will be summarized as medians, ranges, and IQRs. The *T* test and nonparametric analysis will be applied to analyze continuous variables with normal and nonnormal distributions, respectively, and categorical variables will be analyzed by the *χ*
^2^ test or Fisher’s exact test. *P* < 0.05 will indicate a statistically significant difference.

If it is limited to a single missing item, the missing data will be estimated from the given mean values. Imputation will not be attempted if the missing data include the whole table or more than one item. A sensitivity analysis will be performed to determine whether the method used to deal with missing data is appropriate.

According to the analysis of 1534 laparoscopic total hysterectomies by the Netherlands prospective cohort study [17], the surgical time is influenced by the uterine weight and the methods of hysterectomy, and the independent risk factors for surgical conversion are body mass index (BMI), uterine weight, laparoscopic hysterectomy method, and age. The stratified randomization of uterine weight will be conducted. Moreover, the BMI and age subgroups will be evaluated.

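### The uterine-size stratification factor is stated in three ways that do not agree, and the stated primary test does not use it

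*Protocol article*

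**What the plan says.** Four places in the protocol article bear on the factor.

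- **Abstract, Methods.** "Stratified randomization will be performed according to uterine size (< 10 cm, 10–15cm, ≥ 15 cm", where the bracket lists the three classes.
- **Randomization and blinding.** "Prior to randomization, all qualified participants will be classified according to uterine size by ultrasonic measurement". Class A is below 10 cm. The middle class is given as "class B = uterine size between 10 and 15 cm of the maximum diameter". For the top class the section has this definition: "class C = uterine size larger than 15 cm of the maximum diameter". The same section calls uterine size the primary determinant of operation time.
- **Statistical analysis.** It cites a cohort study in which "the surgical time is influenced by the uterine weight and the methods of hysterectomy", and then says of this trial: "The stratified randomization of uterine weight will be conducted". For continuous variables it names a t test if normally distributed and a nonparametric test otherwise. No stratum term is mentioned. BMI and age are to be examined as subgroups.
- **Outcome measures.** The baseline list includes "age, BMI, volume of the uterus, concomitant medications". Volume is a characteristic to be recorded; it is not called a stratification factor.

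The Discussion section on confounding calls uterine size the main confounder and says that the stratified design is there to remove its influence. The Participants section admits all uterine sizes.

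**The concern.** A stratification factor has to be one variable with classes that do not overlap, because it decides which allocation list a patient is drawn from. Here the class limits differ between two sections, and a third section names a different variable. Someone working from the abstract and someone working from the randomization section could assign the same patient to different strata. A later reader could not tell from the article which variable and limits were used.

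The analysis raises a related point. The trial goes to the trouble of balancing the arms on the factor it regards as most important for its primary outcome, and then names a primary test that ignores that factor. When a design is stratified on a prognostic factor, an unadjusted test remains valid. It leaves the between-stratum variation in the error term, however, so its standard error tends to be too large and precision already paid for is given up.

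**Working it through.** **Step 1: apply both sets of limits.** The inputs are the class limits in the abstract and in the randomization section. The latter's middle class is read as including its end points, since otherwise 10 cm and 15 cm would belong to no class.

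| Maximum diameter | Randomization section | Abstract |
|---|---|---|
| 9.9 cm | A | A |
| 10 cm | B | B |
| 14.9 cm | B | B |
| 15.0 cm | B | B and C |
| 15.1 cm | C | C |

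Only exactly 15 cm is ambiguous. The abstract overlaps with itself there, and its top class differs from the randomization section.

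**Step 2: compare the named variables.** The randomization section gives a variable (maximum diameter), a method (ultrasound), a time (before randomization) and cut-points. The sentence in the Statistical analysis section gives a variable (weight) and none of the other three. The two cannot both describe the same randomization. Only the first can be carried out as written.

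**Step 3: check whether the sample size depends on this.** Inputs from the Sample size calculation section: means 170.1 and 125.72 min, SDs 49.97 and 51 min, two-sided alpha 0.05, power 0.9.

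- Difference: 170.1 − 125.72 = 44.38 min.
- Pooled SD: √((49.97² + 51²)/2) = 50.49 min.
- The normal approximation gives 28 per group. The t-test solution is 28.19, rounded up to 29, which is the plan's figure.
- Inflation: 29 × 1.15 = 33.35, rounded up to 34, again the plan's figure.

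The stratification factor enters none of these steps, so the contradiction does not change 29, 34 or 68.

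**Step 4: what adjustment could gain.** The documents do not say how much of the variance in operation time the strata explain. Call that share R², as an assumption. With 34 per arm and balance within strata, the standard error of the difference is about 50.49 × √(1 − R²) × √(2/34), where √(2/34) = 0.2425.

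| Assumed R² | Residual SD (min) | Standard error (min) |
|---|---|---|
| 0 | 50.49 | 12.25 |
| 0.1 | 47.90 | 11.62 |
| 0.2 | 45.16 | 10.95 |
| 0.3 | 42.24 | 10.24 |

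The price is two degrees of freedom for three strata (68 − 2 = 66 becomes 68 − 4 = 64), which is negligible. The range only illustrates the size of the gain; the protocol's own description of uterine size suggests that R² is not zero.

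**The case against.** The strongest reply is that these are wording slips. The randomization section is the operative text and the abstract only a summary. The word weight was probably carried over from the cohort study cited just before it, and the abstract, the Participants section, the randomization section and the Discussion all speak of uterine size. A 15 cm uterus placed in either class is still allocated at random with equal numbers planned per arm, so no bias arises. Most of this stands, and it limits the weight of the point. It does not remove the contradiction: the randomization sentence in the Statistical analysis section is wrong as written.

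A second reply is that stratum adjustment is usually settled in the statistical analysis plan. That would answer a complaint about silence. Here, though, the article names the tests, and they are unadjusted. If a separate plan already adjusts, the article should be brought into line with it.

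A reader might infer more than the documents support:

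- **Volume as a third definition of the factor.** It is only a baseline characteristic, and recording it does not conflict with stratifying by diameter.
- **All 68 patients analysed by the wrong variable.** The sentence on weight concerns randomization. No planned analysis uses weight, and weight is not among the data listed for collection.
- **The trial cannot be stratified as planned, because weight is known only after surgery.** That is a reasonable inference, but the documents do not say it, and diameter is available before randomization in any case.
- **Diameter and stratum go unrecorded.** Every participant is classified before randomization, and an article need not list every case report form field.

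**Conclusion.** The point holds as an inconsistency in how the factor is stated, together with a primary test that leaves the factor unused. The wording part has small consequences: one ambiguous diameter value, no allocation bias, no change in sample size. How many patients have a uterus recorded as exactly 15 cm is not given; rounding to whole centimetres would raise the number. The documents give no stratum sizes either, so a claim that a few such patients would unbalance the top class cannot be supported.

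The analysis part is a matter of efficiency, not validity. Its size depends on the unknown share of variance explained by the strata. Under the assumed range up to 0.3, the standard error falls from 12.25 to 10.24 min at most. This rests on the plan's SDs, which come from two separate sources, and on reasonable balance within strata.

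**What to change.** 1. State one factor, preoperative ultrasound maximum diameter, with non-overlapping limits. Use the same wording in the abstract, the Randomization and blinding section and the Statistical analysis section. Recruitment began on July 1, 2021, so the side on which 15 cm falls should follow the randomization list actually in use and should not be changed midway.
2. In the Statistical analysis section, replace uterine weight by this factor in the randomization sentence. The account of the cited cohort can stay as it is.
3. Analyse total operation time with adjustment for the assigned uterine-size stratum: for example, a linear model with arm and stratum or, if the distribution is clearly non-normal, a stratified rank test. Use the stratum from which the patient was randomized. Fix this before the data are analysed.

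The cost is a few sentences and one extra term in the model. No new measurement and no additional patients are needed, because the ultrasound classification already takes place before allocation.

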### Recruitment and eligibility

Recruitment started on July 1, 2021. Patients who plan to undergo total hysterectomy will be enrolled.

Only qualified women who provide informed consent before randomization can be included in the trial. The recruitment of the required sample size (*N* = 68) can be completed within 1 year, followed by 6 months of follow-up and a 6-month analysis/reporting period, for a total of approximately 2 years for the whole process.

### Measurement and data collection

#### Outcome measures

The following baseline characteristics of patients will be documented: age, BMI, volume of the uterus, concomitant medications, EQ-5D scores, and anesthesiology scores (ASA).

B. The specific process for follow-up (Table 1):

During the screening period (before surgery), surgical indication, inclusion and exclusion indicators, gynecological check results will be investigated.

The collection of data on the day of surgery will include the successful removal of the uterus by the technique as randomized; conversion to laparoscopy or laparotomy; the total operation time (classified as the single-port establishment time, pelvic-abdominal adhesion release time, total hysterectomy time, specimen removal time, and stump suture time); estimated blood loss; intraoperative complications (including blood transfusion, vascular repair, bowel surgery, bladder surgery, ureter operation); and surgeon fatigue.

On the day of discharge, data on hospitalization expenses and the postoperative hospital stay will be collected by the research assessor.

During the 8 weeks after the intervention, postoperative complications (such as a second operation, infection, urogenital tract injury, intra-abdominal hemorrhage, incision hematoma, incision infection) will be recorded and rated by the Clavien–Dindo classification method. Health-related quality of life (EQ-5D) will be assessed again at 8 weeks (Table 2).

**Table 2 Tab2:** Patient’s characteristics and data collection

Timepoint	Study period							
	Enrollment	Allocation	Post-allocation					Close-out
		0	Pre-operation	Operation	Post-operation	Discharge	After 8 weeks	

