#### Secondary objectives

Single-port establishment time, pelvic-abdominal adhesion release time, total hysterectomy time (including salpingectomy or appendectomy time), specimen removal time, and vaginal stump suture timeSurgical conversion rate (switching to another LESS technique) and transfer rate (converting LESS surgery to traditional laparoscopy/laparotomy)Estimated intraoperative blood lossIntraoperative and postoperative complications (Clavien–Dindo grade≥ II级)Score for health-related quality of life (EQ-5D)Economic benefits with respect to hospitalization expensesPostoperative hospital staySurgeon fatigue

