### Sample size calculation

The sample size was calculated on the basis of the primary outcome, namely, the total operation time. Current reports on the “cross technique” for LESS-TH show that the average operation time is 170.1 ± 49.97 min [15]. According to our pilot retrospective study of 46 patients undergoing LESS-TH with the “chopstick technique,” the average operation time was 125.72 ± 51 min. The difference between the average values of the two operation time was determined as the minimum difference. A bilateral difference test was used. The first-order risk (*α*) is 0.05, and the power (1-β) is set at 0.9 for the study. Based on the evaluation of PASS 25.0 statistical software, each group requires 29 patients. The study consists of equivalent numbers for each treatment arm. In consideration of the loss to follow-up and multiple surgeons’ influences on the operation time, the sample size was expanded by 15% to 34 patients for each group. A total of 68 patients are required for the experiment.

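### EQ-5D is measured before surgery and at 8 weeks, but the stated analysis does not adjust for the preoperative score and so gives up some precision on a secondary outcome

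*Protocol article*

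**What the plan says.** The protocol article lists the EQ-5D score among its secondary objectives. Under Outcome measures it is collected at baseline: "The following baseline characteristics of patients will be documented: age, BMI, volume of the uterus, concomitant medications, EQ-5D scores". The same section adds that "Health-related quality of life (EQ-5D) will be assessed again at 8 weeks". Table 2 agrees, marking EQ-5D before the operation and after 8 weeks.

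The Statistical analysis section has one rule for comparing continuous outcomes. It pairs the t test with a rank-type alternative: "nonparametric analysis will be applied to analyze continuous variables with normal and nonnormal distributions, respectively". EQ-5D is not mentioned there, and neither is a change score, a regression model or a baseline covariate. Patient characteristics enter that section in two ways only. Uterine weight is named as a randomization stratum, and for the others the text says "Moreover, the BMI and age subgroups will be evaluated".

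**The concern.** The trial collects each patient's EQ-5D score before surgery, and the only comparison it states makes no adjustment for it. Part of the spread in 8-week scores will reflect where patients started. A plain two-group test leaves that part in the error term. Randomization is stratified on uterine size alone, so it does not directly balance baseline EQ-5D.

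At stake is the width of the EQ-5D interval, with 34 patients per arm at most. The sample size was set for operation time, and the article gives no power or precision target for EQ-5D.

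**Working it through.** **The plan's own figure.** The only sample size in the article is for total operation time. The inputs in Sample size calculation are 170.1 (SD 49.97) min against 125.72 (SD 51) min, two-sided alpha 0.05 and power 0.90.

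- Difference: 170.1 − 125.72 = 44.38 min.
- Pooled SD: √((49.97² + 51²)/2) = 50.49 min.
- The normal approximation gives 28 per group. The t-based solution gives 28.19, rounded up to the stated 29.
- Inflation: 29 × 1.15 = 33.35, rounded up to the stated 34 per group, 68 in total.

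The figure reproduces. It concerns operation time, and nothing below changes it.

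**Assumed input.** The correlation ρ between preoperative and 8-week EQ-5D is not in the document. I take 0.3 to 0.6 as an assumption.

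**Variance of the treatment comparison, relative to a t test on the 8-week score (= 1).** The change-score column assumes equal SDs at the two times.

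| ρ | t test on 8-week score | t test on change, 2(1 − ρ) | Baseline-adjusted, 1 − ρ² |
|---|---|---|---|
| 0.3 | 1 | 1.40 | 0.91 |
| 0.5 | 1 | 1.00 | 0.75 |
| 0.6 | 1 | 0.80 | 0.64 |

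The change score never beats adjustment: 2(1 − ρ) − (1 − ρ²) = (1 − ρ)², which is positive for every ρ below 1. Below ρ = 0.5 it is also worse than ignoring the baseline. So the unstated choice between 8-week score and change does not remove the loss.

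**Size before the cost of estimation.**

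- ρ = 0.3: variance falls by 9% and the standard error by 1 − √0.91 = 4.6%. 68/0.91 ≈ 75, so 68 patients act like about 75.
- ρ = 0.6: variance falls by 36% and the standard error by 1 − √0.64 = 20%. 68/0.64 ≈ 106.
- For an illustrative difference of 0.5 SD at 34 per arm, power is 54% unadjusted, 58% at ρ = 0.3 and 73% at ρ = 0.6.

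**Cost of the extra coefficients.** At 34 per arm, one added coefficient inflates the variance by about 1/(68 − 4) = 1/64 = 1.6%. Baseline EQ-5D plus a three-level size class adds three coefficients, so at most about 3 × 1.6% ≈ 5%. The cost is lower where stratification balances the size classes. Taking the full 3/64 = 4.7%:

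- ρ = 0.3: 0.91 × 1.047 = 0.95, a net fall of about 5%.
- ρ = 0.6: 0.64 × 1.047 = 0.67, a net fall of about 33%.
- Break-even against the 8-week t test: (1 − ρ²) × 1.047 = 1, so ρ ≈ 0.21.

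**Loss to follow-up.** If only 29 per arm are assessed at 8 weeks, the factors 1 − ρ² do not change. The cost per coefficient becomes 1/(58 − 4) = 1.9%, or up to 5.6% for three.

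**The case against.** The strongest objection is that the article never says which EQ-5D variable enters the test. A t test on change from baseline fits the text and uses the preoperative score. This stands against the stronger reading that the plan discards the baseline, which a reader might infer but the text does not establish. It does not remove the point, because a change score is still less precise than adjustment.

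A second objection is that covariates for a secondary outcome are usually set in a statistical analysis plan, which is not shown. That is partly fair. But the article is not silent here: it fixes the test for all continuous variables, and that test is unadjusted. If a fuller document already specifies an adjusted EQ-5D model, the point is met and the article's wording only needs to match it.

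Third, the size rests on an assumed correlation. It also applies to the t test only. If the scores are skewed and the nonparametric test is used, 1 − ρ² does not describe the planned comparison. Both remarks stand, so the figures are illustrative. It is also tempting to argue from the range of indications, fibroids to early cancer, that baseline quality of life must vary widely. No EQ-5D data in the document support that, and the point does not need it.

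Finally, the stakes are low. EQ-5D is one of several secondary outcomes in a trial that calls itself exploratory. That stands, and it limits the priority.

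**Conclusion.** The point holds as a matter of precision. The trial records a preoperative EQ-5D score, and the only analysis stated for continuous outcomes does not adjust for it. Under ρ of 0.3 to 0.6, an assumption, adjustment lowers the variance against a t test on the 8-week score by 9% to 36% before costs. After the largest likely cost at 34 per arm, the fall is about 5% to 33%: small at the lower end, material at the upper. Below ρ of about 0.21 the three-coefficient model could gain nothing over that t test.

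A reader might go further and infer that chance baseline imbalance biases the EQ-5D comparison or invalidates the test. The documents do not support that. Under randomization the unadjusted test is valid, and its interval already allows for such imbalance. The primary outcome and the total of 68 are unaffected. This is a worthwhile improvement to a secondary analysis and does not correct an error in the trial's main conclusion.

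**What to change.** Add one sentence to Statistical analysis: the 8-week EQ-5D score will be analysed by linear regression on arm, preoperative EQ-5D score and uterine-size class, reporting the adjusted mean difference with a 95% confidence interval, using robust standard errors or a bootstrap if scores are skewed. This also settles which EQ-5D variable is analysed before the data are seen.

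The cost is that sentence. The preoperative score and the size class are already collected, so no visit, measurement or patient is added. If the model is already written in a document not shown, bring the article's sentence into line with it.
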